#### **Statistical Interim Analysis, Data Review and Stopping guidelines**

Registration and assessment data are captured online via Qualtrics. Participants are assigned a unique code for all data files and audio tapes. Access to the system is restricted to named study personnel and via password protection. The University of Oxford's (UO) IT services have arranged for the files to be encrypted and backed up on a weekly basis. The data are copied to separate tapes, that are inaccessible without the TSM database by the UO IT Services. Papers from clinical interviews are kept in locked cabinets at UO. The audiotapes from clinical interviews are backed up online with password-protection and access restricted to study personnel. The blood samples are centrifuged as soon as the laboratory at the University of Surrey receives them on the day of collection. Saliva samples are analysed at the University of Surrey by RIA analysis.

In line with the OCTRU and the Medicines for Human Use Clinical Trials Regulations (2004), we have not recruited a Data Monitoring Committee because recruitment and follow-up occur over a short period, there are minimal risks to participants and the trial protocol is not modified regardless of any interim data. No interim analyses are planned.

#### **Timing of Final Analysis**

Originally, as stated in the published trial protocol ([name] et al., 2018), we had planned to analyse the trial data once the trial was finished at two year follow-up. However, the outbreak of the Covid pandemic may have added additional risk to the mental health of emergency workers and therefore, if iCT-R leads to improvement in emergency workers' mental health compared to Mind-Online or Standard Treatment, it would be beneficial to roll out the intervention as soon as possible. It has been discussed and agreed with the Trial Steering Committee that data could be analysed early, namely after completion of the 1-year follow-up period, if rates of PTSD and MDD diagnoses in the total sample at 1-year follow-up are higher than expected. At 1 year follow-up, in the total sample, rates of PTSD are 8.7% compared to 8.3% in non-intervention studies of this population [1] and the general population rate of 3%. Rates of depression are 15.8% compared to 10.6% in non-intervention longitudinal studies of this population [1] and the general population rate of 10.3%. Since

there are higher than expected rates of PTSD and MDD diagnoses at 1-year follow-up in the total sample we now plan to analyse data at 1-year follow-up. Two-year follow-up data (including sub-thresholds) will be analysed by including them into the 1-year outcome models once they have been completed.

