### 11.2 The Number of Participants

We plan to recruit 570 participants.

The risk of student paramedics developing full syndromal PTSD and MD over two years without intervention is 10% (1), and 25% if subsyndromal PTSD and MD that cause significant distress are included. We predict that our intervention will reduce the relative risk by 50%. Setting power at 80%,  $\alpha=.05$  and hypothesizing a reduction of relative risk of 50% gives an odds ratio of 0.429, which requires a total sample size of N=304 to show a risk reduction of 50% between the active and placebo intervention. Thus, each condition would require N=152. Since we have a third condition (no-training control), the total sample size required would be N=456. Allowing for a 20% rate of attrition, we will require a total sample size of N=570.

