## **Statistical Analysis Outline**

Linear and logistic mixed effects modelling are used to test the primary and secondary trial objectives (with the exclusion of the health economic analyses, which will be conducted by [name] and therefore not part of this analysis plan, as well as the hormone and immune function analyses which will be conducted by Professors [name] and [name]), which is the standard technique for analysing clinical trials.

For the primary and secondary trial objectives, 1-year follow-up is the short-term primary outcome time point (except for immune and hormone function for which the time-point is post-intervention), PTSD and MDD diagnoses are the primary outcome measures. Once completed, the 2-year PTSD and MDD diagnoses at 2-year follow-up are the long-term and main primary outcome time points.

Both repeated assessments and intervention arm are specified as categorical variables for reasons of flexibility in the modelling approach. Repeated assessments, intervention arm, their interaction effects, and baseline scores and covariates are estimated as fixed effects and random effects are estimated for time (level 1) nested within the participants (level 2). An unstructured variance-covariance matrix is used to model the error correlation structure within the participants.

Global comparisons for the main effect of intervention group and the interaction effects between time and intervention group are tested for primary and secondary trial objectives and further group comparisons are carried out if the global comparisons are significant. The hierarchy of the group comparisons reads as follows: 1) iCT-R versus Mind-Online, 2) iCT-R versus Standard Practice, and 3) Mind-Online versus Standard Practice. Site is introduced as a random effect in the analyses of the primary trial objectives. If non-significant, site will not be carried forward into further trial analyses.

Maximum Likelihood estimation is used. Assumptions for mixed effects modelling are tested and normality of residuals are confirmed for the outcome measures. If assumptions are violated, resampling approaches will be used.

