## **STATISTICAL PRINCIPLES**

### **Statistical Significance and Multiple Testing**

In the case of different scaling, continuous variables are standardized for the analysis. Global comparisons are tested and if significant, group comparisons are then carried out.

[name], [name], [name], [name], [name], [name], [name], [name], [name], [name], [name], & [name] Cognitive resilience training to prevent PTSD and MDD in paramedics: A randomised controlled trial.

If not specified otherwise, one or the other, main effects of intervention group or interaction effects between intervention group and time in favour of iCT-R, indicate intervention superiority.

All analyses will be carried out with a significance level of  $p < .05$ , two-sided.

No adjustments for multiple testing are made, as the primary trial objective is to evaluate any superiority in efficacy of the new resilience intervention compared to the existing online intervention (group comparison between these two groups of highest priority and directive hypothesis).

Confidence intervals are reported at the 95% level, two-sided.

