#### **Description of Compliance with Intervention**

Level of compliance will be defined as 1) number of online modules completed during the intervention, 2) practice of tools.

A complier-average causal effect analysis (CACE) is used to test any influence of compliance on the intent-to-treat intervention effect of the primary trial objective analyses.

1067

1068

1069 **Reliability**

1070           The primary outcome measures, such as Structured Interviews by clinicians and self-  
1071 reports for the primary outcomes and nearly all of the secondary outcome measures are  
1072 standard instruments that have been validated and have shown good reliability.

1073           Scoring is done as described in the manuals or publications for the measures and  
1074 relevant sub-scales and Cronbach's Alphas are reported for the study sample.

1075           Interrater-reliability is reported for 1-year follow-up data. 10% of diagnoses at 1-year  
1076 follow-up are rated by a second rater.

1077           To ensure consistency in the data, validation checks on the data are carried out before  
1078 locking the dataset and analysis of the data. These include checking for potential data entry  
1079 mistakes, duplicate records, checking the range of variable values, missing data value codes,  
1080 etc.

1081 **ANALYSIS**

1082 **Outcome Definitions**

1083 Outcome measures:

1084           The primary outcome measure for the primary trial objective is PTSD and MDD  
1085 diagnoses (SCID-5;). Secondary outcomes with regards to the primary trial objective are  
1086 PTSD symptom severity (PCL-5) and MDD symptom severity (PHQ-9).

1087

1088           Outcome measures for the secondary trial objectives include resilience measures  
1089 (Wagnild-Resilience Scale and CD-RISC, both continuous), well-being measures (subscale  
1090 rumination of the RIQ, GAD-7, GHQ-12, WEMWBS), general health measures (weight and  
1091 height; Insomnia severity index; Smoking Behaviour Questionnaire, sum score for both  
1092 items; Alcohol Use Questionnaire, unit increase/ decrease/ stayed the same), health economic  
1093 costs (intervention costs per QALY gained based on 4 measures), and hormone and immune  
1094 function (collected with saliva samples and CRP plasma).

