## **Analysis Methods**

Analyses of the primary trial objectives:

To analyse any differences between the intervention arms in terms of effectiveness with regards to rates of PTSD and MDD diagnoses (SCID-5) at 1-year follow-up (short-term primary outcome time point) and at 2-years follow-up (long-term primary outcome time point once completed), intervention condition and the interaction between intervention time and

intervention group on rates of PTSD and MDD diagnoses, logistic mixed effects models with PTSD and MDD diagnoses as outcomes (short-term outcome 1-year follow-up data, long-term outcome 2-years follow-up once completed) are specified and analysed.

To analyse any differences between the intervention arms in terms of effectiveness with regards to PTSD symptom severity (PCL-5) or MDD symptom severity (PHQ-9) at 1-year follow-up (short-term primary outcome time point) and at 2-years follow-up (long-term primary outcome time point once completed), intervention condition (categorical; iCT-R versus Mind-Online versus Standard practice; level 2) and the interaction between intervention time (categorical; post-intervention, 6-months follow-up; 1-year-follow-up, 2-year follow-up, once completed; level 1) and intervention group on PTSD or MDD symptom severity, linear mixed effects models with either PTSD or MDD symptom severity as outcomes are specified and analysed.

Both repeated assessments and intervention arm are specified as categorical variables for reasons of flexibility in the modelling approach. Repeated assessments/ time, intervention arm, both their interaction effects, and baseline scores and covariates are estimated as fixed effects and random effects are estimated for time (level 1) nested within the participants (level 2). An unstructured variance-covariance matrix is used to model the error correlation structure within the participants. Estimation method is Maximum Likelihood. Normality of the residuals for the outcomes is confirmed visually.

Randomisation has been done by stratification by site, gender, and baseline PTSD symptom severity and MDD symptom severity. Therefore, baseline PTSD symptom severity and MDD symptom severity and randomisation factors are added as covariates in these models. Site is added as random factor in those models. If non-significant, they will not be carried forward into further analyses.

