In case of a significant main effect of intervention group or interaction effect between intervention group and time with regards to the primary outcome measure (PTSD and MDD diagnoses) and secondary outcome measures for the primary trial objective (PTSD and MDD symptom severity), intervention group comparisons are carried out using pairwise contrasts. iCT-R (coded as '1') is tested against Mind-Online (coded as '0') and a significant main effect or interaction in favour of iCT-R indicates intervention superiority (comparison of highest priority) of the newly developed resilience intervention over the existing online intervention. In a second step, iCT-R (coded as '1') is then tested against Standard Practice

(coded as '0') and again, a significant main effect or interaction in favour of iCT-R indicates intervention superiority for the newly developed intervention over usual Standard Practice. In a third step, Mind-Online (coded as '1') is tested against Standard Practice (coded as '0') and a significant main effect or interaction in favour of Mind-Online indicates intervention superiority of the existing online intervention compared to Standard Practice.

Adjusted/ estimated mean differences and Cohen's d's with standard deviation at baseline in the denominator are reported in tables for continuous outcomes for the intervention effects from results of linear mixed effects models and frequencies of diagnoses (absolute numbers and percentages) and absolute values as well as estimated/ adjusted odds ratios are reported for dichotomous outcomes.

All significance tests are carried out on a  $p < .05$  level, two-sided, and confidence intervals are reported on the 95% level.

Analyses of secondary trial objectives:

Any intervention effects on the secondary outcome measures, such as resilience (Connor-Davidson Resilience Scale,; Wagnild Resilience Scale), rumination (ruminative responses brooding subscale; Responses to Intrusions Questionnaire rumination subscale), anxiety (GAD-7), Smoking Behaviour (Smoking Behaviour Questionnaire), Alcohol consumption (Alcohol Use Questionnaire), psychological distress (GHQ), well-being (Warwick Edinburgh Mental Wellbeing Scale), sleep quality (Insomnia severity index), and weight, are analysed for the short-term primary outcome time point of 1-year and for the long-term primary outcome time point of 2-years follow-up, once completed.

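### SAP 3.5 puts two-year data with undefined sub-threshold cases into one-year models of full diagnoses; the case definition at the main time point is unsettled and, taken literally, changes with visit

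*Combined protocol and SAP*

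**What the plan says.** Three sets of statements bear on what counts as a case.

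- **SAP 3.5, Timing of Final Analysis:** "Two-year follow-up data (including sub-thresholds) will be analysed by including them into the 1-year outcome models once they have been completed". This is the SAP's only mention of sub-threshold cases. It gives no definition and ties them to the two-year data.
- **SAP 3.7, 6.1 and 6.2:** the outcome is diagnoses. SAP 3.7 states "Once completed, the 2-year PTSD and MDD diagnoses at 2-year follow-up are the long-term and main primary outcome time points". SAP 6.1 (Outcome Definitions) states "The primary outcome measure for the primary trial objective is PTSD and MDD" diagnoses on the SCID-5. SAP 6.2 specifies "logistic mixed effects models with PTSD and MDD diagnoses as outcomes" for both the one-year and the two-year time point. None of these includes sub-threshold cases.
- **Protocol synopsis and objectives table:** the primary objective counts subsyndromal PTSD and MD at follow-up and does not restrict them to a visit. Protocol 11.2 gives the two-year risk without intervention as 10% for full disorder and "25% if subsyndromal PTSD and MD that cause significant distress are included".

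On testing, SAP 3.7 says "Global comparisons for the main effect of intervention group and the interaction effects between time and intervention group are tested", with pairwise contrasts to follow. Under SAP 4.1, "main effects of intervention group or interaction effects between intervention group and time in favour of iCT-R, indicate intervention superiority". SAP 6.2 repeats this for iCT-R against Mind-Online: "a significant main effect or interaction in favour of iCT-R indicates intervention superiority (comparison of highest priority").

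**The concern.** If the sentence in SAP 3.5 is carried out as written, the repeated binary outcome is full diagnosis at 6 and 52 weeks, and full or sub-threshold at 104 weeks. A participant who is sub-threshold at both 52 and 104 weeks is then scored 0 and 1, an apparent new case. A participant who improves from full disorder to sub-threshold is scored 1 and 1, and the improvement is hidden.

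Inside such a model, visit and definition are perfectly confounded, and no term can separate them. The pooled group effect averages odds ratios for two different outcomes. The group-by-time term, which the SAP accepts as evidence of superiority, mixes change over time with any difference between the effects on full and sub-threshold cases.

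Timing adds to this. The one-year analysis is run first, so an unresolved definition for the main time point would be settled with one-year results already in hand. The choice also determines whether the planned sample size is adequate.

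**Working it through.** **Inputs.** Protocol 11.2: 10% full disorder, 25% including subsyndromal, 50% relative reduction, odds ratio 0.429, 80% power, alpha 0.05, 304 for two arms, 456 for three, 570 after 20% attrition. SAP 4.1: two-sided tests. SAP 3.5: observed one-year rates in the total sample of 8.7% PTSD and 15.8% depression.

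**1. The plan's own figure.** Two proportions, two-sided, pooled variance, no continuity correction, 25% v 12.5%:

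n = [1.96 × √(2 × 0.1875 × 0.8125) + 0.842 × √(0.25 × 0.75 + 0.125 × 0.875)]² / 0.125² = 151.9, so 152 per arm.

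Then 2 × 152 = 304, 3 × 152 = 456, and 456 / 0.80 = 570. The odds ratio is (0.125/0.875) / (0.25/0.75) = 0.429. All stated figures reproduce, but only at the 25% rate that includes subsyndromal cases.

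**2. Time term, literal reading, no real change between visits.**

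- Control: (0.25/0.75) / (0.10/0.90) = 3.00. That is 152 × 0.15 = 22.8 extra cases per 152.
- iCT-R at half the risk: (0.125/0.875) / (0.05/0.95) = 2.71.
- With 15.8% at one year in place of 10%, holding 25% fixed: (0.25/0.75) / (0.158/0.842) = 1.78. Depression alone was 15.8%, so the rate of either disorder is at least that and 1.8 is an upper limit.

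**3. Group-by-time term.** Ratio of odds ratios (ROR) = two-year OR / one-year OR. With 5% v 10% full disorder at one year, the OR is (0.05/0.95) / (0.10/0.90) = 0.474. At two years control is 25%, and iCT-R is 5% plus 15% × RR, where RR is an assumed effect on the extra sub-threshold risk.

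| RR on sub-threshold cases | iCT-R at two years | Two-year OR | ROR |
|---|---|---|---|
| 0.25 | 8.75% | 0.288 | 0.61 |
| 0.50 (the planned reduction, uniform) | 12.5% | 0.429 | 0.90 |
| 0.75 | 16.25% | 0.582 | 1.23 |
| 1.00 | 20% | 0.750 | 1.58 |

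With no intervention effect on either case type, both odds ratios are 1 and so is the ROR. For the uniform 50% row, log ROR = −0.10. Treating visits as independent at 152 per arm, SE = √[1/(152 × 0.25 × 0.75) + 1/(152 × 0.125 × 0.875) + 1/(152 × 0.10 × 0.90) + 1/(152 × 0.05 × 0.95)] = 0.55, so z is about −0.2.

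**4. Power under each single definition, 152 per arm.**

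- Full or sub-threshold, 25% v 12.5%: 80.0%.
- Full diagnoses, 10% v 5%: z = [0.05 − 1.96 × √(2 × 0.075 × 0.925/152)] / √[(0.10 × 0.90 + 0.05 × 0.95)/152] = (0.05 − 0.0592) / 0.0301 = −0.31, so 38%. It is 45.6% at 190 per arm (570/3, no attrition). Reaching 80% would need 435 per arm.
- Full diagnoses at an assumed control rate of 15.8%, v 7.9%: z = [0.079 − 1.96 × √(2 × 0.1185 × 0.8815/152)] / √[(0.158 × 0.842 + 0.079 × 0.921)/152] = (0.079 − 0.0727) / 0.0368 = 0.17, so about 57%.

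**The case against.** **The sentence is ambiguous.** SAP 3.5 is a section on timing. It speaks of models in the plural. It does not say that a sub-threshold result is coded as a case in the diagnosis model, nor that such results are ignored at one year. It could mean a further outcome, modelled in the same way. The sections that define the analysis name diagnoses at both time points. A reader might infer that the SAP has settled on a definition that changes with visit; the documents do not support that. What survives is that the only sentence on the matter puts these data into the one-year models, no separate model is described, and the sections disagree.

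**The group-by-time term does not simply measure the change of definition.** That stronger reading, with frequent false superiority as its consequence, is tempting but wrong in general. Two-arm, two-visit simulations (4,000 trials, 152 per arm, 30% to 90% of participants keeping their status) gave 5% to 6% rejection under the planned uniform 50% reduction; with no intervention effect rejection is about 4%. Rejection rose to 31% to 55% only when iCT-R was assumed to leave full cases at 10% and cut subsyndromal cases from 15% to 5%. It was 30% to 41%, as an apparent loss of effect, when iCT-R was assumed only to move full cases to subsyndromal. With three arms and three visits, these became 28% to 49% and 25% to 27%. No document suggests either pattern. In the first, iCT-R really does reduce subsyndromal cases, which the protocol's objective counts as benefit.

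**The time odds ratio is not a test of superiority.** Superiority rests on group or group-by-time. The 3.0 also treats two-year risks as rates at each visit, and the observed one-year rates point to a smaller figure. Both points stand.

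**Conclusion.** The point holds as an internal contradiction with a faulty rule if followed literally, and I rate it as should-fix. SAP 3.5 conflicts with SAP 3.7, 6.1 and 6.2 on the outcome at the main time point, the protocol's objective differs again, and the SAP leaves sub-threshold undefined.

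On the literal reading, the time term is distorted whether or not iCT-R works. The treatment comparison is at risk only through an effect that differs by severity: the artefact is nil with no effect, negligible under the planned uniform reduction, and material in either direction otherwise. Nothing in the documents rules such a difference in or out. It would therefore be wrong to conclude that the plan will produce a false claim of superiority.

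The consequence for power does not depend on the literal reading. The planned 304 belongs to the definition that includes subsyndromal cases, whereas SAP 3.3 (Sample Size) attaches it to diagnoses without giving a control rate.

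These figures assume the protocol's 10% and 25% for PTSD and MD combined, used as rates at each visit, and the stated range for the effect on sub-threshold cases. They are marginal rates; participant-specific odds ratios from the mixed model would differ in size but not in direction.

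**What to change.** Replace the sentence in SAP 3.5 so that each model uses one case definition at 6, 52 and 104 weeks:

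1. Add the two-year full SCID-5 diagnoses to the full-diagnosis models.
2. Fit a separate model to full-or-sub-threshold status, coded by the same rule at every visit.
3. Define sub-threshold PTSD and sub-threshold MDD in SAP 6.1.
4. Name which of the two is primary before the two-year analysis, align SAP 3.3, 3.7, 6.1 and 6.2 and the protocol objective with it, and state the power for that choice with its control rate.

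The cost is SAP wording and one extra model. Protocol Appendix B already schedules the SCID PTSD and MD modules at 6, 52 and 104 weeks, so no new visits are needed. Sub-threshold status must be coded at the earlier visits, which is possible only if the SCID records hold enough detail; the documents do not say. If full diagnoses are made primary, the stated power will be less favourable than 80%. If sub-threshold cases are included, N=570 stands as calculated.

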## **Blinded analysis**

No blinded analyses are to take place prior to the final data lock currently planned.

